#### Adverse events

Adverse events will be recorded in Castor EDC [31] and checked regularly by the research physician. The accredited medical ethical committee will be notified in the case of serious adverse events. All adverse events will be followed up until they have abated or until a stable situation has been reached.

### Statistical analysis plan

All data will be treated according to the General Data Protection Regulation Act (EU GDPR) and will be collected using Castor EDC [31]. Analyses will be performed in R version 4.1.0. Prior to the analysis, group allocation will be blinded to the members of the research team that will perform the statistical analysis. Descriptive statistics will be used to explore and present baseline characteristics of the study population. Continuous data will be presented quantitatively as means and their 95% confidence intervals or, when not normally distributed, as median [interquartile range]. Categorical data will be presented as counts and percentages. Data will be analysed according to the intention-to-treat principle.

Independent samples t-tests will be performed to analyse the difference in change of thigh muscle volume and the difference in mixed MPS between groups VEG and OMNI and between groups VEG and VEG-RE. Data will be checked for normality using QQ-plots. Missing data may be imputed via multiple imputation or the related data may be eliminated. In case of a non-normal distribution, non-parametric tests will be used or data will be log-transformed. Furthermore, linear mixed models will be used to assess the differences between these groups for the other outcome measures. Participants will be added to the model as random factors. Treatment and timepoint will be added as fixed factors as main effects and their interaction. A maximum of three potential confounding factors may be added to each model as fixed factor. Model assumptions will be checked using QQ-plots and scatterplots. A two-sided p-value < 0.05 will be considered statistically significant. The Benjamini-Hochberg correction will be applied to adjust for multiple testing. In case more than two time points are tested and a significant treatment*time interaction is observed, a post-hoc analysis for will be performed using a Bonferroni correction.

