**Methods:**

Seventy-two community-dwelling individuals aged ≥ 65 years with a BMI between 23 and 32 kg/m^2^ will be included in this randomized controlled trial. Eligible participants will be randomly allocated to either follow their habitual omnivorous diet, a self-composed vegan diet, or a self-composed vegan diet combined with two sessions of RE per week for 12 weeks. Participants will be guided through monthly nutrition information meetings. Dietary intake and physical activity levels will be assessed using food records and accelerometery. The primary study outcome will be thigh muscle volume, assessed at baseline and after 12 weeks using magnetic resonance imaging (MRI). Secondary outcomes will be: body composition, muscle fat infiltration, muscle strength, bone mineral density, bone turnover markers, metabolic profile, insulin levels, cobalamin, iron and vitamin D status, hs-CRP, gut metabolomics and metagenomics, gastro-intestinal symptoms and dietary intake. Measurements will take place at baseline, after 6 weeks, and after 12 weeks. Additionally, mixed muscle protein synthesis rates will be assessed during the first ten days of the intervention using a deuterium oxide protocol. Data will be analysed using independent t-tests and linear mixed models.

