#### Sample size calculation

The sample size calculation was based on the primary outcome and was performed in GPower version 3.1.9.4 (Düsseldorf, Germany). Since the current study aims to compare the effect of a vegan diet to an omnivorous diet on thigh muscle volume, and to compare the effect of a vegan diet to a vegan diet in combination with RE on thigh muscle volume (two different contrasts), the sample size calculation was based on testing change in thigh muscle volume between two group comparisons. A separate two-tailed α-level of 0.05 was used for each contrast. A mean change of 4% in thigh muscle volume was expected in the vegan group. The latter was based on previous studies that assessed changes in thigh muscle volume during caloric restriction in middle aged to older adults, as no study has previously assessed the effect of a vegan diet on thigh muscle volume. Reductions in thigh muscle volume of ~ 6.5% were previously observed following a year of caloric restriction [27, 28]. Others additionally observed that the largest decline in thigh muscle volume presented itself during the first three months of caloric restriction [29]. Additionally assuming an expected reduction in the consumption of protein with a concurrent reduction in protein quality [10, 30], a mean change of 4% in thigh muscle volume was expected on the vegan diet in the present study. Using an expected mean change of 4% and standard deviation of 5% [10, 27–30], and 80% power, a total of 60 participants, 20 per group, will need to be included in the study. Considering a drop-out rate of 20%, 24 participants per group will be recruited, leading to a total of 72 participants.

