#### Randomization

Following inclusion, participants will be randomized to one of the three study arms on a 1:1:1 ratio, using block randomization with variable block sizes of 3, 6 and 9 to ensure equal allocation to each group. Randomization will be stratified for gender and partners will be randomized together. The randomization will be performed in Castor EDC by a member of the research team [31]. Considering the logistics of the study procedures, both the members of the research team and the participants will be aware of the group allocation.

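### The primary t-tests on change omit gender, the stratification factor, and do not adjust for baseline volume as a covariate: valid, but power is lost if gender predicts change

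*Protocol article*

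**What the plan says.** All references are to the protocol article.

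- **Statistical analysis plan, primary outcome and mixed MPS:** "Independent samples t-tests will be performed to analyse the difference in change of thigh muscle volume and the difference in mixed MPS between groups". The contrasts are VEG against OMNI and VEG against VEG-RE. No covariate is named for these tests.
- **Randomization:** "Randomization will be stratified for gender and partners will be randomized together".
- **Abstract, Methods:** thigh muscle volume is "assessed at baseline and after 12 weeks using magnetic resonance imaging (MRI)", so a baseline value is planned for everyone.
- **Statistical analysis plan, remaining outcomes:** "linear mixed models will be used to assess the differences between these groups for the other outcome measures". These models hold participant as a random factor, and treatment, timepoint and their interaction as fixed factors. In addition, "A maximum of three potential confounding factors may be added to each model as fixed factor". The factors are not named, and the text does not say that they must be measured before randomisation.
- **Sample size calculation:** "A separate two-tailed α-level of 0.05 was used for each contrast". The inputs are these: "Using an expected mean change of 4% and standard deviation of 5% [10, 27–30], and 80% power, a total of 60 participants, 20 per group".

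**The concern.** Stratified allocation balances gender across arms, so gender contributes little to the true variability of the difference between arms. A two-sample t-test does not know this. It leaves whatever gender explains of the change in the error term, so its standard error is too large and its interval too wide. The analysis should normally contain the factor on which allocation was stratified, and here that costs nothing to collect.

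Baseline volume is a lesser matter. The change score fixes the baseline slope at 1 instead of estimating it, which is less efficient whenever the correlation between the two scans is below 1.

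The protocol's own inputs leave no power to spare. A null result from a conservative test could be read as reassurance about muscle loss on a vegan diet.

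For the other outcomes the covariate rule is open. The trial records diet, body mass and physical activity during the intervention. Protein intake is part of the hypothesised pathway, so adjusting for it would remove part of the diet effect that the model is meant to estimate.

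**Working it through.** **Inputs from the protocol:** difference 4%, SD of change 5% (d = 4/5 = 0.8), two-sided α 0.05 per contrast, 20 evaluable per arm, 24 recruited per arm.

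**Assumptions (not in the protocol):** share R² of the variance in change explained by gender, 0 to 10%; between-person coefficient of variation (CV) of thigh muscle volume, 15–25%.

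**1. The protocol's own figure.** SE = 5 × √(2/20) = 1.58 and noncentrality = 4/1.58 = 2.53 on 38 df. Power is 69%, not 80%. With 24 per arm (46 df) it is 77%, and 26 per arm are needed for 80%. The stated 20 per arm therefore does not reproduce under the stated two-sided α. That is a separate point about sample size; here it only shows that there is no slack.

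**2. Gender and baseline in the model.** Residual SD = 5 × √(1 − R²); noncentrality = 4 / (residual SD × √(2/20)). With two covariates, a per-contrast model has 40 − 4 = 36 df and a three-arm model has 60 − 5 = 55 df.

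| R² | SE | Power, per contrast (36 df) | Power, three arms (55 df) |
|---|---|---|---|
| 0 | 1.58 | 69.2% | 70.0% |
| 0.05 | 1.54 | 71.4% | 72.2% |
| 0.10 | 1.50 | 73.7% | 74.5% |

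At R² = 0 the three-arm model gains 0.7 points over the t-test, purely from degrees of freedom.

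**3. Is the t-test conservative?** Simulation with arms of 20, balanced on gender: if gender explains 5%, 10% or 20% of the variance in change, the t-test's true type I error is about 4.4%, 4% and 3%. Its power stays at 70–71%. If gender explains nothing, type I error is 5% and power 69%. So the error is always towards caution, and it vanishes at R² = 0.

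**4. The baseline slope.** With equal variances at both scans, ρ = 1 − 0.05²/(2 × CV²). Adjusting for baseline instead of subtracting it multiplies the variance by (1 + ρ)/2.

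| CV | ρ | Variance ratio | Reduction |
|---|---|---|---|
| 15% | 0.944 | 0.972 | 2.8% |
| 20% | 0.969 | 0.984 | 1.6% |
| 25% | 0.980 | 0.990 | 1.0% |

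In the three-arm model this moves power from 70.0% to about 70.4–71.2%.

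**5. Chance baseline imbalance.** The slope of change on baseline is −(1 − ρ). An imbalance of one standard error in baseline means, CV × √(2/20), shifts the estimated difference by (1 − ρ) × CV × √(2/20). That is 0.056 × 4.74 = 0.26 percentage points at CV 15%, and 0.020 × 7.91 = 0.16 at CV 25%. Both are small beside an effect of 4 and an SE of 1.58.

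**6. Pooling variance over three arms.** If training raised the SD of change in VEG-RE to 7% (assumption), the pooled SD would be √((25 + 25 + 49)/3) = 5.74. The VEG–OMNI standard error would be 5.74/5 = 1.15 times its proper value. An ordinary pooled model is therefore not a free gain.

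**The case against.** A t-test on change is a legitimate analysis of a randomised trial, and it matches the basis of the sample size calculation. It uses baseline by subtraction, does not bias the estimate, and does not inflate type I error through the omission of gender. The only gain of any size needs gender to predict the change, and nothing in the protocol says that it does. The model does not restore 80% power at 20 per arm under the range assumed here. Partners are allocated together; positive correlation within couples would push the standard error the other way, so the net direction of the error is not established. All of this stands. It limits the point to efficiency, but it does not defend leaving the stratification factor out of a named primary test.

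Three stronger readings might be inferred, and the protocol supports none of them.

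- **That baseline is ignored.** It is not; the outcome tested is the change.
- **That the primary result is biased or invalid.** Omitting gender makes the test at worst conservative, and steps 4 and 5 show that little hangs on the baseline slope.
- **That the mixed models will adjust for mediators.** The text speaks of potential confounders, caps them at three, and blinds the analysts to allocation. It nowhere says that post-randomisation variables will be used, and a full analysis plan may name the covariates. What remains is that the rule as worded does not exclude them, and blinding would not prevent the bias if they were used.

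**Conclusion.** The point holds as a matter of efficiency and conservatism in the primary test. With 20 per arm, a 4% effect and a 5% SD, the cost is 69–70% power against 71–74% (per contrast) or 72–75% (three arms, equal variances) if gender explains 5–10% of the variance in change. There is no loss if it explains none. The gain from the baseline slope is 1–3% of variance, given a between-person CV of 15–25%. The gender share and the CV are both assumptions. For the other outcomes the point is narrower: gender is not among the stated model terms, and the covariate rule should be closed to variables measured after randomisation.

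**What to change.** - **Thigh muscle volume:** replace the t-tests by a linear model of week-12 volume (or change) on arm, baseline volume and gender. Report VEG versus OMNI and VEG-RE versus VEG with 95% confidence intervals. Fit it either per contrast or as one three-arm model with standard errors that allow unequal arm variances.
- **Mixed MPS:** use arm and gender.
- **Sensitivity analysis:** keep the unadjusted t-test.
- **Mixed models:** include gender and limit any further covariates to baseline variables, so that protein intake or weight change during the intervention is not adjusted for. Add the baseline outcome as a covariate only if baseline is removed from the response timepoints; otherwise the same measurement stands on both sides of the model.

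The cost is a few sentences of analysis wording. The variables are already collected, and recruitment and visits do not change. This does not settle the sample size discrepancy or the joint allocation of partners, which need their own treatment.

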#### Bone mineral density and bone turnover markers

Bone mineral density (BMD; g/cm^2^) will be measured at baseline and after 12 weeks using Dual X-Ray Absorptiometry (DEXA; GE Healthcare Prodigy Pro). Participants will be instructed to lie down on a table and to remain motionless during the scan. First, a total body scan will be performed to assess total body and spine BMD. Subsequently, a separate scan of each hip will be made. Additionally, blood samples will be collected at baseline, after 6 and after 12 weeks in EDTA containing tubes to assess the levels of insulin-like growth factor 1 (IGF-1), parathyroid hormone (PTH), bone resorption marker cross-linked C-telopeptide of type I collagen (CTX) and bone formation marker procollagen type I N-propeptide (PINP). Since CTX levels are highly affected by circadian rhythm, time of blood sampling will be the same for each subject and each measurement, and before 10 am [39]. The EDTA containing tube will be centrifuged for 15 min at 1000 g and 4 ˚C to obtain plasma aliquots. Plasma CTX, PINP, IGF-1 and PTH levels will be assessed using a chemiluminescent immunoassay. Plasma PTH levels will be analyzed on the same day as blood collection.

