#### Blood pressure

Systolic and diastolic blood pressure (mmHg) will be assessed at baseline, after 6 and 12 weeks. The measurement will be performed after an overnight fast using an ambulatory blood pressure monitor (Omron Healthcare Europe B.V.; OMRON automatic digital blood pressure monitor HEM-907; CE-certified). Participants will be instructed not to drink coffee, smoke or perform vigorous exercise in the 60 min before the measurement and will not be allowed to speak during the measurement. Blood pressure will be measured three consecutive times with 1 min rest intervals, after resting on a chair for 5 min. The mean of the second and third measurement will be used for analysis. A fourth measurement will be performed if the participant speaks or moves during a measurement or when a difference of 10 mmHg is observed between the second and third measurement. In those cases, the mean of the third and fourth measurement will be used for analysis.

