#### Dietary assessment

Dietary intake will be assessed before the start of the intervention, at the beginning of the intervention, approximately halfway, and at the end of the intervention via three-day food records. The food records will be administered via a dietary assessment smartphone application (Traqq) [43]. The food records will cover two weekdays and one weekend day for each assessment period, which will be randomly assigned to each participant at each assessment period to allow for an even spread of dietary assessment throughout the week. Participants will receive a notification once in the morning on the day that they are assigned to report their dietary intake. After reporting of the food products, participants will be requested to enter the consumed amount and the eating occasion. The computation module of Compl-eat [44] will subsequently be used to calculate intake of food groups, energy, macro- and micronutrients by multiplying consumed amounts by energy or nutrient content using the Dutch Food Composition Database 2021, extended with the products that will be provided to the participants in this study. In case a participant has no (compatible) smartphone, the participant will list his or her dietary intake on a paper food diary, which will subsequently be transferred to Compl-eat by a member of the research team. Participants will be contacted for clarifications in case of obscurities in the dietary data. All records will be checked by a member of the research team for completeness, unusual consumed amounts, and notes.

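### For outcomes with three or more visits, the stated participant random factor imposes equal correlation between visits; if correlation decays with time, the 12-week contrast gets too small a standard error

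*Protocol article*

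**What the plan says.** All places are in the protocol article. Under Statistical analysis plan, thigh muscle volume and mixed muscle protein synthesis are compared by t-tests. For the rest, "linear mixed models will be used to assess the differences between these groups for the other outcome measures". The model is given term by term: "Participants will be added to the model as random factors. Treatment and timepoint will be added as fixed factors as main effects", together with their interaction. No other within-participant covariance device is named, and none is excluded. Assumptions are to be checked by QQ-plots and scatterplots.

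On testing, the section says "A two-sided p-value < 0.05 will be considered statistically significant" and adds a Benjamini-Hochberg adjustment. With more than two time points, a Bonferroni-corrected post-hoc analysis follows only if the treatment-by-time interaction is significant. It does not say whether the week-12 comparison is a difference in change or a difference in level.

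Several outcomes have three or more visits:
- Bone turnover markers: "blood samples will be collected at baseline, after 6 and after 12 weeks in EDTA containing tubes".
- Blood pressure: "Systolic and diastolic blood pressure (mmHg) will be assessed at baseline, after 6 and 12 weeks".
- Insulin and metabolic profile: the same three visits (Metabolic profile and hs-CRP).
- Dietary intake: "before the start of the intervention, at the beginning of the intervention, approximately halfway, and at the end of the intervention".
- Body mass: baseline, week 6 and week 12 after screening (Other study outcomes); Table 2 adds day 10.

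Table 1 asks for the 12-week effect of the vegan diet against the omnivorous diet, and of the vegan diet with exercise against the vegan diet alone, on bone turnover markers, metabolic profile and insulin among others.

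**The concern.** A random intercept lets participants differ in level and treats what remains as independent noise of constant size. Every pair of visits then has the same correlation, and every change the same variance, whether it spans 6 weeks or 12. If baseline and week 12 are less alike than adjacent visits, the true 12-week change is more variable than the model allows. The model gives that change the average variance over all pairs of visits.

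The 12-week effect is the one Table 1 asks for. At stake are p-values that are too small and intervals that are too narrow for the multi-visit secondary outcomes. The planned residual plots do not directly test whether correlation is equal across visits, so the problem could pass unnoticed.

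**Working it through.** **Inputs.** From the article: 20 evaluable participants per arm, three arms, two-sided 5%, visits at 0, 6 and 12 weeks. The article gives no variance, correlation or standard error for any repeated outcome, so there is no figure of its own to reproduce. The correlations below are assumptions, shown as a range.

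**Formula.** With complete data and unit variance, the change between visits j and k has variance 2(1 − r_jk). The random-intercept model uses the mean of this over all pairs. So

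SE ratio (model / true) = sqrt[ mean over pairs of 2(1 − r_jk) / 2(1 − r_0,12) ],

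and the large-sample type I error of an unadjusted 5% test of the 12-week difference in change is 2[1 − Φ(1.96 × ratio)].

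**Worked case, adjacent correlation 0.8 and 12-week correlation 0.64.** The three change variances are 0.40, 0.40 and 0.72, with mean 1.52 / 3 = 0.507. Ratio = sqrt(0.507 / 0.72) = 0.839. Error = 2[1 − Φ(1.644)] = 10.0%.

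**Range at three visits:**

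| Assumed pattern | SE ratio | Type I error |
|---|---|---|
| Equal correlations | 1.00 | 5.0% |
| Stable person effect plus weak decay (0.76 / 0.728) | 0.960 | 6.0% |
| First-order autoregressive (AR) decay plus 30% measurement noise | 0.92-0.97 | 5.7-7.1% |
| AR decay, 0.5 between adjacent visits | 0.882 | 8.4% |
| AR decay, 0.8 | 0.839 | 10.0% |
| AR decay, 0.9 | 0.827 | 10.5% |
| Both changes from baseline correlated 0.8, weeks 6 and 12 correlated 0.7 | 1.080 | 3.4% |
| Week 6 the odd visit (0.6 with both others, which correlate 0.8) | 1.291 | 1.1% |

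The limit as AR decay approaches 1 is about 11%. Simulation of the balanced random-intercept test in three arms gave 4.8% under equal correlation, and 8.2%, 9.8% and 10.1% for AR decay 0.5, 0.8 and 0.9. With four visits (days 0, 10, 42, 84) and AR decay 0.5-0.9 per six weeks, the formula gives 10.8-13.5%.

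**Intervals.** In the AR rows for 0.5-0.9, nominal 95% intervals for the 12-week change cover 100 − 8.4 = 91.6% down to 100 − 10.5 = 89.5%.

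**With the planned sequence** (interaction p < 0.05, then the change contrast at 0.025, Bonferroni for two tests), 20 per arm:
- *No arm differs.* AR decay 0.5-0.9 gives a week-12 false-positive rate of 2.2-2.8% in a three-arm model and 4.0-5.1% in a two-arm model. The interaction test itself runs at 5.4-6.0%.
- *Exercise arm differs, the two diet-only arms do not.* AR decay 0.6-0.9, true week-12 effect in the exercise arm of 1.0-1.5 SD of change: the gate opens in 90-99.9% of trials. The null vegan-omnivorous contrast is then rejected in 5.0-6.6% at nominal 2.5%, and in 2.9-4.0% at nominal 1.25% (four tests). Under equal correlation the first rate is the nominal 2.5%.

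**The case against.** The strongest objection is that the article does not plan the ungated, unadjusted 5% test behind the table. When no arm differs, the interaction gate and Bonferroni step keep the week-12 error at or near 5% or below in these three-visit AR cases. That stands. It fails once a real exercise effect opens the three-arm gate. The introduction hypothesises an exercise effect for thigh muscle volume only; that it extends to the multi-visit outcomes is plausible but an assumption. Benjamini-Hochberg takes the p-values as given, and no gate widens an interval.

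Second, the correlations are unknown. A reader might infer that every multi-visit outcome is tested at about double the nominal level. The documents do not support that: about 10% needs strong decay and an ungated change contrast. Equal correlation gives 5%, measurement noise brings the rate near 6-7%, and other patterns make the test conservative.

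Third, if the comparison is the group difference in level at week 12 with equal variances over visits, error is 5.2-5.6% in simulation, close to nominal. The article leaves this open.

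Fourth, an article may leave covariance structure to a fuller plan. Silence would indeed be no finding. But here the model is listed term by term, and the one device listed carries the equal-correlation assumption.

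Fifth, the affected outcomes are not primary. Body mass is explorative, and the dietary objective in Table 1 is descriptive. This limits the weight of the point.

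**Conclusion.** The point holds as a conditional one and is worth correcting. Taken at face value, the stated model is right for three or more visits only if variances and correlations are equal across visits, which nothing in the article supports. If correlation decays with time, the unadjusted type I error of the 12-week change contrast is roughly 6-11% at three visits, with intervals narrow to match. If the exercise arm alone differs and decay is strong, a Bonferroni test at 2.5% runs at about 5-6.6%. If correlation is equal there is no error, and the direction can reverse.

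These figures assume 20 complete participants per arm, a plain random intercept and a difference-in-change contrast. Thigh muscle volume and mixed muscle protein synthesis are analysed by t-test and are untouched. So are outcomes measured only at baseline and week 12 (MRI, DEXA, Biodex), because with one pair of visits there is nothing to average over.

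**What to change.** For outcomes with three or more visits, replace the participant random factor by an unstructured within-participant covariance (six parameters for three visits), with Kenward-Roger or Satterthwaite degrees of freedom. State that the 12-week difference in change is estimated from that model. In R this can be done with the mmrm package. Keep the random intercept for two-visit outcomes.

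The unstructured form is valid whichever correlation pattern holds, so no correlation has to be guessed beforehand. The cost is a sentence or two in the plan, a small change of code, a few more variance parameters and slightly fewer degrees of freedom. Design, visits and sample size do not change.
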